#### **Data collected for long-term follow-up:**

#### **Performance of NLP**

[name] lab at DFCI has published several studies on the use of NLP to capture documentation of ACP in clinical notes.(91 – 93) Compared to standard medical record review her team has achieved a sensitivity 97% - 99% and specificity 85% - 100% at the note level. At the patient level, both sensitivity and specificity are close to 100%. Patients accrue hundreds to thousands of notes which makes standard medical review not feasible, and this method dramatically increases efficiency and sensitivity.

Advances in computer science techniques such as NLP allow for efficient and accurate analysis of the free-text from clinical notes in order to detect our primary outcomes. The increasing use of EHR combined with computational advances in NLP can accurately quantify our primary outcome.

The below procedures will be completed at Northwell Health by the respective site-Investigators. No patient identifiable information will leave the HIPPA-secure firewall of the health care system.

Each site-Investigator will use NLP to identify the following primary outcome.

Data will be abstracted from the EHR data repository. Demographic information and baseline characteristics relevant will be collected. Analysis of free text regarding ACP will be extrapolated using computational methods.

[figure not shown]

Individual variables have been selected as they are basic demographic and baseline characteristics of study participants.

The Investigators will use computational methods (NLP) to identify our outcomes. Once these variables have been abstracted from the health care system's EHR, the data will be collected for each patient and the patient will be given a random unique identifier. A cross-walk of the unique identifier and the identifiable information of the patient will be securely stored at the health care system and not transferred to DFCI.

The deidentified data for each patient will then be sent to DFCI and MGH for further analysis.

Only researchers listed on this IRB will be able to access the data. The risks will be minimal as the data will be stored and analyzed on the HIPAA secure cluster at each health care system. None of the data will be stored in paper form. The data and identifiers will be kept for three years on the HIPAA secure cluster computer. After the three years, the data will be permanently destroyed.

## 10.0 Data and Specimen Banking

NA

## 11.0 Data Management and Confidentiality

### DATA ANALYSES

**Aim 1:** To test the combined effects of an ACP Program on rates of ascertainable quality measures of ACP among 13,000 patients at risk or with COVID-19. We will use an intention to treat approach. All patients over 65 engaged with the clinic over the course of each time period in each of the three study periods will be included in the analysis. We will use generalized linear mixed models to compare outcomes between intervention and the two control periods. The basic model is depicted in Equation (1)

$$g(Y_{ijk}) = \mu + \alpha_i + \beta_j + \gamma_k + X_{ik} \theta \quad (\text{Eq 1})$$

where  $Y_{ijk}$  denotes the response from individual  $k$  from cluster (PCP)  $j$  at period  $i$ . The model includes a fixed effect  $\alpha_i$  for period  $i$ , which indicates the difference between periods. Our primary comparison is between the post-intervention period and the two control periods. The model also includes a random effect  $\beta_j$  for cluster  $j$  to take into account the patients within PCP clustering. It is likely a large proportion of patients will overlap in the adjacent study periods; therefore, the model includes a random subject effect  $\gamma_k$  for individual  $k$  to take into account the repeated measures from the same subject. We will limit the analysis to those who appear in two or more comparison

[figure not shown]

periods as a secondary analysis. The model also includes an additional term of  $X_{ik}$  which represents the patient characteristics at period  $i$  to adjust for potential confounding factors. We will use a logit link ( $\mathcal{G}$ ) for the binary outcomes which include our primary outcome of ACP documentation.

**Sample Size Calculation & Power Analysis:** We estimated approximately 7,800 patients from 150 PCPs are eligible for the study at each period and 85% patients overlap from one period to the next. With 3 time periods, we anticipate a total of 10,139 unique patients will be included in the study. For our primary comparison between COVID-19 period and post intervention period, we expect 7,800 patients in each of the two periods with 6,630 appearing in both periods. In the most conservative scenario with each PCP contributing an average 44 patients, the design effect is 3.2 assuming an intra-cluster correlation of 0.05, which corresponds to an effective sample size of 2,098 appearing in both periods. Preliminary estimates indicate the rate for ACP documentation (primary outcome) is around 10% pre-COVID and 20% during COVID. The study will have more than 95% power to detect a 5% absolute increase in outcome with a two-sided significance level of 0.05. The power will be even higher for a 10% post intervention increase, which is our threshold of a clinically meaningful difference.

**Exploratory Aim:** To examine facilitators and barriers to intervention success, we will conduct a qualitative analysis of interview transcripts collected from 30 participating clinicians. An examination of their perceptions of the training and video intervention, as well as facilitators and barriers to implementation will help to contextualize, and possibly explain, the trial findings.

**Aim 2:** To characterize ACP documentation rates among under-represented minority groups. The analysis will use a difference in differences approach comparing the changes from the control period to the intervention period between White and non-White racial minority and between non-Medicaid and Medicaid patients. This will translate into adding a subgroup fixed effect to (Eq 1) and test the interaction between period and subgroups. We will explore the intervention effect in each racial minority (Black, Hispanic, Asian) separately.

**Sample Size Calculation & Power Analysis:** Preliminary estimates indicate 30% of the population is non-white racial minority and approximately 30% of the population were on Medicaid. Assuming the rate for ACP documentation is 21.5% among Whites and 16.5% among non-White (overall 20%) during COVID, and both groups increase to 30% post-intervention, our simulation study shows that we will have >90% power to detect a 5% difference in differences after taking into account of clustering. We anticipate a larger difference in differences between Medicaid and non-Medicaid patients; therefore, the power for that analysis will be even higher.

[figure not shown]

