We will train 150 primary care clinicians caring for 13,000 diverse patients over the age of 65 from Northwell Health, a health care system in which we are already embedded with our ongoing grant. We will use Natural Language Processing (NLP) to abstract patient outcomes from the Electronic Health Record (EHR). *We hypothesize that a telehealth ACP Program will improve and sustain rates of ACP from the time that the intervention is implemented (11/01/2020 through 04/30/2021) compared to two time periods prior to the intervention: Pre-COVID-19 (09/15/2019 – 03/14/2020) and during the COVID-19 surge (03/15/2020 – 09/14/2020). The six weeks in between our intervention period and the COVID-19 surge period represents our start-up period for the intervention, also known as a “washout” period.*

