### Specific Aims:

**Aim 1:** To test the combined effects of an ACP Program on rates of ascertainable quality measures of ACP. We will conduct a Pre-Post, open-cohort design, pragmatic trial with 150 clinicians and evaluate the effectiveness of the intervention by comparing ACP documentation among **13,000 patients over 65**. **Hypothesis:** *A higher proportion of*

[figure not shown]

*patients in the intervention period (vs. control period) will have ACP documentation (primary trial outcome).*

**Aim 2:** To characterize ACP documentation rates among under-served minority groups.

**Hypothesis:** *Under-served minorities in the intervention period will have fewer disparities in ACP documentation.*

**Exploratory Aim:** Qualitative assessment of barriers and facilitators for intervention success. *Our goal is to identify and describe clinician implementation experiences .*

**IMPACT:** COVID-19 poses a unique dilemma for older Americans, who must balance their desire to live against the risk of a lonely and traumatic hospital death. Clinician communication training and video decision support is a practical, evidence-based, and innovative approach to assist patients facing this most difficult of all choices. Major strengths of this proposal are: the highly experienced team making this project feasible; the present infrastructure already embedded at Northwell Health; and, the potential immediate deployment of the intervention, if successful, across the country. This work holds the promise of improving the quality of care provided to millions of Americans during the COVID-19 pandemic.

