A Pre-Post, open-cohort, pragmatic trial is well-suited to evaluate an ACP Program intervention in older patients during the COVID-19 pandemic: Several notable advantages of this design exist for testing communication interventions in older patients during a pandemic.(88-91) In response to COVID-19 and the increased mortality, we expect that Northwell Health ACP activity increased naturally. Two six-month control periods prior to the wide-scale implementation of the intervention, allow us to measure a baseline rate of ACP activity and identify the “pre-COVID-19 ACP baseline rate” and a “COVID-19 ACP baseline rate.” We chose September 15, 2019 as the start of the pre-COVID-19 control period since it is about one year before the intervention start, and we chose March 15, 2020 as the start of the baseline control period since the earliest ACP activities due to COVID-19 began during that month.(92, 93) We will then compare the ACP rate during the implementation period, which begins November 1, 2020 and continues for six months, to the rates in the previous two control periods. Given that the intervention is entirely online, no logistic barriers prohibit us from training providers on a shortened timeline.(94) Clinicians will be trained during the early weeks of the trial, avoiding any contamination during the control period. In addition, the low-risk intervention being tested will be implemented at the clinic level and our ongoing study received IRB-approval exempting it from individual consent procedures when using an open-cohort design. Thus, the proposed trial is an optimal design for a COVID-19 study and a logical next step toward understanding the real-world application of the Comprehensive ACP Program. Taken together, this work has the potential to improve the quality of care provided to millions of older Americans during the COVID-19 pandemic.

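### The protocol defines its primary comparison in two ways: against both control periods in the analysis section, and against the COVID-19 period alone in the power calculation

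*Protocol*

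**What the plan says.** Protocol section 11.0, Data Analyses, Aim 1, sets out a logistic mixed model with a fixed effect for each of the three periods and then says: "Our primary comparison is between the post-intervention period and the two control periods". The Sample Size Calculation & Power Analysis paragraph for the same aim begins its power argument with "For our primary comparison between COVID-19 period and post intervention period, we expect 7,800 patients in each of the two periods", and its effective sample size and power refer to that contrast alone.

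The rest of the protocol does not settle the matter. Section 1.0 frames the overall hypothesis as improvement "compared to two time periods prior to the intervention". Sections 2.0, 8.0 and 9.0 also describe comparison with both earlier periods. The Aim 1 hypothesis under Specific Aims and the Aim 2 analysis text each refer to one control period without naming it.

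On the expected rates, the sample size paragraph says: "Preliminary estimates indicate the rate for ACP documentation (primary outcome) is around 10% pre-COVID and 20% during COVID". Section 2.0 gives the reason: "In response to COVID-19 and the increased mortality, we expect that Northwell Health ACP activity increased naturally".

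**The concern.** The two statements define different hypotheses under one label. A contrast that draws on the pre-COVID period takes in some or all of a 10-point rise that the plan itself attributes to the pandemic, before any clinician was trained. A contrast with the COVID-19 period alone does not. The protocol also does not say whether comparison with two control periods means one pooled or averaged contrast, two tests of which either suffices, or two tests that must both succeed. At stake is whether a positive primary result could be claimed when documentation had merely stayed at its COVID-19 level. This is more than detail that a statistical analysis plan might supply, because the protocol states the primary contrast twice and the two statements conflict.

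**Working it through.** **Inputs, all from section 11.0, Aim 1 sample size paragraph:** 7,800 patients per period; 150 PCPs; 6,630 patients in both periods; intra-cluster correlation 0.05; effective sample size 2,098; rates 10% and 20%; a 5-point detectable increase; two-sided 0.05; power above 95%.

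**Step 1: reproduce the plan's figures.**
- Patients per PCP: 6,630 / 150 = 44.2.
- Design effect: 1 + (44.2 − 1) × 0.05 = 3.16.
- Effective sample size: 6,630 / 3.16 = 2,098, as stated.
- Power for 20% versus 25% with 2,098 per period, treated as independent: 97.3%. A paired calculation with an assumed within-patient correlation of 0 to 0.5 gives 97.2% to 99.98%.

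Both agree with the stated power, so the stated figures belong to the COVID-19-only comparison.

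**Step 2: no intervention effect, with the intervention-period rate set to the COVID-19 rate of 20% (an assumption).** As a simplification, 2,098 effective patients are used in each period and the periods are treated as independent.

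- *Pooled controls.* Mean control rate (10% + 20%) / 2 = 15%, effective n = 2 × 2,098 = 4,196. SE = √(0.20 × 0.80 / 2,098 + 0.15 × 0.85 / 4,196) = 0.0103. z = 0.05 / 0.0103 = 4.84. P(significant) = Φ(4.84 − 1.96) = 99.8%.
- *Controls averaged on the logit scale of Eq 1.* logit(0.20) − ½[logit(0.10) + logit(0.20)] = 0.405, an odds ratio of 1.50. SE = 0.071, z = 5.71, P(significant) = 99.99%.
- *Pre-COVID period alone.* SE = √(0.10 × 0.90 / 2,098 + 0.20 × 0.80 / 2,098) = 0.0109. z = 0.10 / 0.0109 = 9.16, P(significant) about 100%.
- *COVID-19 period alone.* True difference 0, so 2.5% in the favourable direction.
- *Decision rules on two separate tests.* Either suffices: about 100%. Both required: about 2.5%.

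A cluster simulation (150 PCPs, 7,800 / 150 = 52 patients each per period, intra-cluster correlation 0.05, 2,000 runs per setting) gave 100% for the averaged contrast and 2.0% to 2.8% for the COVID-19-only contrast.

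**Step 3: vary the assumed no-intervention rate.** Probability of a positive result with no intervention effect:

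| No-intervention rate | Pooled contrast | Logit-average contrast |
|---|---|---|
| 20% | 99.8% | 99.99% |
| 19% | 98% | 99.7% |
| 18% | 85% | 97% |
| 17% | 53% | 80% |
| 16% | 18% | 43% |
| 15% | 2.5% | 11% |

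The contrast itself is zero at 15% on the pooled scale and at 14.3% on the logit-average scale.

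**The case against.** A reader might infer that the analysis-section wording would by itself produce a positive trial with no intervention effect. The documents do not support that.

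- **Pooling is not stated.** Eq 1 has a separate effect for each period, and sections 2.0 and 9.0 treat the two baselines as distinct rates. Two separate contrasts from one model is a natural reading, perhaps the more natural one.
- **The rule for combining two contrasts is not stated.** The section 1.0 hypothesis can fairly be read as improvement over both periods. Under that rule the false-positive rate at 20% is about 2.5%.
- **The no-intervention rate is not stated.** The protocol gives no rate expected for November 2020 to April 2021 without the programme. Twenty percent is the surge-period figure carried forward.
- **The 10-point clinical threshold does not carry over.** It appears in the COVID-19 versus post-intervention calculation, so the 10-point gap from pre-COVID should not be presented as meeting it.
- **The design's basis is partly visible.** The power paragraph names its contrast, and the Aim 2 power calculation starts from rates during COVID (21.5% and 16.5%, overall 20%).

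All of these points stand, and they make the false-positive figures conditional. They do not remove the conflict: one section gives two different definitions of the primary comparison, and no text says which governs or that both contrasts must succeed.

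**Conclusion.** The contradiction is real and concerns the definition of the primary test, so the two statements must be reconciled. Its consequence depends on the reading. With the intervention-period rate at 20% and no intervention effect, the chance of a positive primary result is about 2.5% under the COVID-19-only or both-required readings, and about 99.8% to 100% under a pooled, averaged or either-suffices reading. The high figures rest on documentation staying near 20% without the intervention. They weaken steadily below that, and for the pooled contrast they reach the nominal 2.5% at 15%.

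**What to change.** In section 11.0, Data Analyses, Aim 1, replace the sentence on the primary comparison with text to this effect: the single primary comparison is the intervention period versus the COVID-19 period (15 March to 14 September 2020), two-sided 0.05; the pre-COVID period is not pooled with it, and intervention versus pre-COVID is supportive. Name the same control period in the Aim 1 hypothesis and the Aim 2 analysis text. This costs a few sentences and no power, since it is the only Aim 1 contrast that was powered.

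Alternatively, if both periods are to remain primary, state that both contrasts must be significant at two-sided 0.05. This costs almost nothing in power. At 10%, 20% and 25%, the pre-COVID contrast has SE = √(0.10 × 0.90 / 2,098 + 0.25 × 0.75 / 2,098) = 0.0115 and z = 0.15 / 0.0115 = 13.0, so its power is practically 100% and joint power stays about 97%.

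Neither option removes secular change after September 2020. That limit belongs to any pre-post comparison and should be acknowledged when the result is interpreted.

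### Eq 1 has no PCP-by-period term, so if PCP documentation rates shift unequally between periods, the standard error of the period effect is too small

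*Protocol*

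**What the plan says.** Section 11.0 (Data Analyses, Aim 1) writes the model as g(Y_ijk) = μ + α_i + β_j + γ_k + X_ik θ with a logit link, for period i, PCP j and patient k. The fixed effect α_i is the quantity of interest, "which indicates the difference between periods". The PCP term β_j carries no period index and is there "to take into account the patients within PCP clustering". The subject term γ_k carries no period index either and is there "to take into account the repeated measures from the same subject". The text states no interaction of PCP with period, no random period slope and no robust variance.

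The power paragraph under Aim 1 takes "approximately 7,800 patients from 150 PCPs are eligible for the study at each period" and 85% overlap between periods. It then applies clustering to the comparison of the COVID-19 period with the post-intervention period: "the design effect is 3.2 assuming an intra-cluster correlation of 0.05". The test is planned "with a two-sided significance level of 0.05".

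**The concern.** A PCP effect that is the same in every period largely cancels when a PCP's patients are compared between periods. Under Eq 1, once the constant PCP and subject effects are accounted for, changes between periods are independent across patients of the same PCP. That holds only if every PCP's rate moves by the same amount on the logit scale, apart from chance.

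Nothing in the protocol supports so uniform a shift. The comparison spans a pandemic surge, during which section 2.0 expects documentation to have risen of its own accord, and the programme works through individual clinicians. If the background change differs between PCPs, patients of one PCP shift together and the information on α_i is limited by the 150 PCPs as well as by the 7,800 patients. Eq 1 cannot represent this. The reported interval for the primary effect would then be too narrow, and the nominal 5% test would reject too often.

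**Working it through.** **The plan's own figures.** 6,630 overlapping patients / 150 PCPs = 44.2 per PCP. Design effect = 1 + (44.2 − 1) × 0.05 = 3.16, stated as 3.2. Effective size = 6,630 / 3.16 = 2,098, as stated. Two-sided power at 0.05 for 20% versus 25% with 2,098 per period is 97.3%, which agrees with the claim of more than 95%.

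**Inputs.** From the protocol: 150 PCPs, m = 7,800 / 150 = 52 patients per PCP and period, overlap 0.85, ICC 0.05, COVID-19 rate 20%. Assumed, because the protocol gives neither: the between-period correlation of PCP effects (r) and the within-patient correlation given the PCP effects (w).

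**Formula.** In units of the outcome variance, the between-period difference in one PCP's mean has variance

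(2/m)(1 − ICC)(1 − 0.85w) + 2·ICC·(1 − r).

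Eq 1 accounts for the first part only. Therefore

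true variance / Eq 1 variance = 1 + m·ICC·(1 − r) / [(1 − ICC)(1 − 0.85w)],

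and the actual size of the nominal 5% test is 2[1 − Φ(1.96/√ratio)].

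Example with r = 0.8 and w = 0: ratio = 1 + 52 × 0.05 × 0.2 / 0.95 = 1.547. The true standard error is 1.24 times the Eq 1 value, and the test size is 2[1 − Φ(1.576)] = 11.5%.

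**Check by simulation.** Eq 1 itself, without covariates, was fitted by maximum likelihood as a logistic mixed model to 1,000 simulated trials per scenario with no true period effect. The last column shows a PCP-level paired t-test on period differences (10,000 trials per scenario), which lets each PCP have its own shift.

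| r | Formula, w = 0 (SE ratio) | Formula, w = 0.5 (SE ratio) | Eq 1 fitted, subject variance 0.5 / 2.0 | PCP-level t-test, 0.5 / 2.0 |
|---|---|---|---|---|
| 1.0 | 5.0% (1.00) | 5.0% (1.00) | 6.3% / 5.5% | 4.9% / 5.1% |
| 0.9 | 8.2% (1.13) | 10.7% (1.21) | 7.4% / 9.0% | 5.0% / 5.0% |
| 0.8 | 11.5% (1.24) | 16.1% (1.40) | 12.1% / 13.8% | 4.9% / 4.9% |
| 0.5 | 20.3% (1.54) | 28.6% (1.84) | 21.5% / 20.7% | 4.9% / 4.8% |

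With 1,000 trials, the Monte Carlo standard error is about 0.7 points at 5% and 1.3 points at 20%. For subject variance 0.5, the average Eq 1 standard error against the empirical one was 0.043 against 0.055 at r = 0.8, and 0.042 against 0.069 at r = 0.5. In the formula, a higher within-patient correlation makes matters worse: it shrinks the part that Eq 1 counts and leaves the omitted part unchanged.

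**Where the planning figure sits.** With m = 44.2, r = 0 and w = 0, the ratio is 1 + 44.2 × 0.05 / 0.95 = 3.33, which equals 3.16 / 0.95. The planned design effect is therefore the r = 0 case. Were it the true inflation, the standard error would be 1.82 times that of Eq 1 and the test would run at about 28%.

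**Power with PCP-by-period variation allowed for.** For 20% versus 25% with w = 0, SE² = [(0.16 + 0.1875) / 7,800] × [0.95 + 2.6(1 − r)]. At r = 0 the SE is 0.01258 and power is Φ(0.05/0.01258 − 1.96) = 97.8%. At r = 0.5 power is 99.9%.

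**Practical reach.** Near a 20% rate, one logit unit is about 0.16 on the probability scale. The smallest significant rise is roughly 1.96 × 0.043 × 0.16 = 1.3 points under Eq 1. With the empirical standard errors it is 1.7 points (r = 0.8) to 2.2 points (r = 0.5). A 5-point rise is 0.288 on the logit scale, so z is about 5.2 and 4.2 with those standard errors.

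**The case against.** The strongest reply is that the size of the problem is assumed. The protocol gives no between-period correlation. At 1.0 Eq 1 is valid, and at 0.9 the excess is modest. This stands, and the point is conditional on unequal PCP shifts.

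A second reply is that the protocol presents Eq 1 as its basic form, so an analysis plan could extend it. This carries little weight: the protocol writes out the random structure, gives a reason for each term, and following it produces the problem.

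A third is that the practical reach is small. Only an observed rise of about 1.3 to 2.2 points would change verdict, whereas the protocol plans for 5 points and regards 10 as clinically meaningful. This also stands for the significance test, though not for the width of the interval.

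A reader might infer more than the protocol supports:

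- **That the power section contradicts Eq 1.** It labels its design effect the most conservative scenario. A pessimistic planning bound does not assert zero correlation. It allows for PCP-level variance that Eq 1 cannot represent, and no more than that.
- **That uneven uptake of training inflates the false-positive rate.** If the programme has no effect on anyone, uneven uptake adds nothing. Only unequal background change does. Uneven uptake bears on interval coverage when there is an effect.
- **That a clinic-level term is required.** Section 2.0 says that "the low-risk intervention being tested will be implemented at the clinic level", but the protocol gives no number of clinics and no clinic-level correlation. Section 9.0 describes small-group training without tying the groups to clinics.
- **That Aim 2 is equally affected.** A shift shared by all patients of a PCP largely cancels from a subgroup comparison within that PCP. The protocol does not say how the subgroups are spread over PCPs, and no calculation supports the extension.

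**Conclusion.** The point holds in conditional form. As written, Eq 1 omits PCP-specific change between periods. If such change exists, the standard error of the period effect is too small. At the protocol's own sizes and ICC, the nominal 5% test runs at about 7–11%, 11–16% and 20–29% for assumed between-period correlations of 0.9, 0.8 and 0.5. Each range spans the formula with within-patient correlation 0 to 0.5 and the direct fits of Eq 1. Perfect correlation, the only case in which Eq 1 is correct, is not supported by anything in the protocol, and the planned design effect already allows for departures from it. The sample size and the power claim are sound. The consequence is an interval that is too narrow and unreliable inference for small differences. The ability to detect a rise of 5 to 10 points is not in doubt.

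**What to change.** Add a random PCP-by-period effect to Eq 1, so that the PCP contribution becomes β_j + (βα)_ij with its own variance. Alternatively, keep Eq 1 and report standard errors that are cluster-robust at PCP level. State which of the two is primary.

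The cost is one variance parameter and somewhat wider intervals: at w = 0, the standard error rises by about 13% if the correlation is 0.9 and by 54% if it is 0.5. No change to the sample size or to the power statement is needed.

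### Aim 2: the stated period-by-subgroup interaction test in a three-period model does not match the two-period difference in differences that the protocol describes and powers

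*Protocol*

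**What the plan says.** All of the relevant text is in Protocol section 11.0, Data Analyses.

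- **Model (Aim 1).** "We will use generalized linear mixed models to compare outcomes between intervention and the two control periods". Eq 1 carries a fixed effect for period and a logit link, and the data come from three periods: "All patients over 65 engaged with the clinic over the course of each time period in each of the three study periods will be included".
- **Aim 2 question.** It is a difference in differences "comparing the changes from the control period to the intervention period between White and non-White racial minority and between non-Medicaid and Medicaid patients". The control period is singular and is not identified.
- **Aim 2 test.** The next sentence reads: "This will translate into adding a subgroup fixed effect to (Eq 1) and test the interaction between period and subgroups". No contrast or degrees of freedom are given.
- **Aim 2 power.** The paragraph gives rates for two periods only: 21.5% (White) and 16.5% (non-White) during COVID, after which "both groups increase to 30% post-intervention". It claims more than 90% power for a 5-point difference in differences. It gives no pre-COVID subgroup rates.
- **Aim 1 does not supply the missing definition.** The model paragraph says "Our primary comparison is between the post-intervention period and the two control periods". The Aim 1 power paragraph instead uses the COVID-19 period alone; its sentence begins "For our primary comparison between COVID-19 period and post intervention period, we expect 7,800 patients in each of the two periods with 6,630 appearing in".

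**The concern.** The described question, the stated test and the powered contrast are three different things. With two periods, a period-by-subgroup interaction is the difference in differences, and the protocol's step from one to the other would be correct. With three periods it is not. The interaction then has two components for each subgroup comparison, and one of them, the change in the gap from pre-COVID to COVID-19, contains no intervention.

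This matters here because the protocol itself expects documentation to rise from about 10% to about 20% between the two untreated periods. A subgroup gap can easily move during such a rise. The Aim 2 hypothesis concerns a smaller disparity in the intervention period. A joint test can be significant because of movement before the intervention, and it has no direction.

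**Working it through.** **Inputs from the protocol.** 7,800 patients per period; 30% non-White, so 5,460 White and 2,340 non-White; overall rate about 10% pre-COVID and 20% during COVID; subgroup rates 21.5%/16.5% during COVID and 30%/30% post-intervention; design effect from an ICC of 0.05. The two-sided 0.05 level is stated for Aim 1 and assumed for Aim 2.

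**Assumptions.** Observations are independent. Pre-COVID subgroup rates are varied around 10% overall, because none are given.

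**Step 1: reproduce the stated power (COVID-19 to post-intervention, 1 df).**
- Overall COVID rate: 0.7 × 21.5 + 0.3 × 16.5 = 20.0%, as stated.
- Risk difference: SE = √(0.215×0.785/5460 + 0.165×0.835/2340 + 0.21/5460 + 0.21/2340) = 0.0148; 0.05/0.0148 = 3.39; power 92%.
- Logit: the COVID gap is logit(0.215) − logit(0.165) = 0.326 and the post gap is 0. The variance of a gap is 1/(5460·pW·qW) + 1/(2340·pN·qN), where q = 1 − p. This is 0.004187 for COVID and 0.002907 post. Noncentrality = 0.326²/(0.004187 + 0.002907) = 15.0; power 97%.

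The stated figure above 90% therefore reproduces, and it belongs to the two-period contrast. Dividing N by the full design effect (1 + 43.2 × 0.05 = 3.16) would give 48% to 59%. That does not show the figure to be wrong, because PCP effects shared across periods and subgroups largely cancel in a difference in differences. A simulation with 150 PCPs and 85% overlap gave 98% to 99.5%.

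**Step 2: hold the gap fixed after the COVID-19 period.** Set the intervention-period rates equal to the COVID-19 rates (21.5%/16.5%). Let the pre-COVID log-odds gap be 0.326 + s, with gap variance V1, and let V2 = 0.004187 for each of the other two periods. The noncentralities are:
- 2-df interaction: s² / (V1 + V2/2)
- Intervention period against the mean of both controls: (s/2)² / (V1/4 + V2/4 + V2)
- Intervention period against COVID-19 only: 0

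Example, s = +0.2: V1 = 0.00840. The 2-df value is 0.04/(0.00840 + 0.00209) = 3.81. The pooled value is 0.01/(0.00210 + 0.00105 + 0.00419) = 1.36.

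| Pre-COVID White/non-White (assumed) | s | 2-df interaction | Pooled controls | COVID-19 only |
|---|---|---|---|---|
| 10.8%/8.1% | 0 | 5% | 5% | 5% |
| 11.1%/7.5% | +0.1 | 13% | 9% | 5% |
| 11.3%/7.0% | +0.2 | 40% | 22% | 5% |
| 10.3%/9.2% | −0.2 | 45% | 22% | 5% |
| 11.5%/6.5% | +0.3 | 73% | 41% | 5% |

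The last row is a special case. Both groups rise by 10 points, so the gap is 5 points throughout and only the log-odds gap moves (0.626 to 0.326). It reflects the logit scale and is not used to size the point.

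**Step 3: sensitivity.** Dividing N by 3.16 divides each noncentrality by 3.16. The +0.1 case falls from 0.99 to 0.31 (rejection 7%), and the −0.2 case from 4.36 to 1.38 (17%). In the other direction, a clustered simulation took an extreme case: no pre-COVID gap (10%/10%), then the same odds-ratio gap in the COVID-19 and intervention periods. The 2-df test rejected 92% to 95%, the pooled contrast 61% to 70% and the COVID-19-only contrast 4.5% to 4.8%.

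**Step 4: cost in power.** On the protocol's own alternative, with a constant control-period gap, power is 98.0% for the 2-df test and 97.2% for the COVID-19-only contrast on the logit scale.

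**The case against.** The test sentence refers back to the one before it, which names a control-to-intervention difference in differences. On that reading the interaction is only the vehicle, and the analyst would extract the relevant contrast. The power paragraph points to COVID-19 versus post-intervention. The fitted model yields the gap in every period, and contrast coding is normally left to a statistical analysis plan, which is not at hand. All of this is fair.

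A reader might infer that the protocol will report an untreated change as an intervention effect. The documents do not support that. No rule says that a joint p-value decides Aim 2, the words joint or omnibus do not appear, and the aim is framed as characterising rates. A reader might also take 73% as the error rate. That case depends on an assumed constant 5-point gap analysed on the logit scale, whereas the protocol states its Aim 2 effect in percentage points.

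What remains is more than missing detail. The protocol does name a test, and that test is not the contrast it describes or powers. Treating the single control period as both controls combined does not remove the problem. Settling the Aim 1 comparator would help, but the Aim 2 sentence would still prescribe the whole interaction.

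It is also true that the COVID-19-only contrast sets aside part of the two-control design and assumes no untreated drift in the gap after that period.

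**Conclusion.** The point holds as a mismatch in the stated plan: Aim 2's test is not fixed to its described and powered question. Both the literal 2-df interaction and the pooled-control reading can reject when the gap did not change between the COVID-19 and intervention periods. For log-odds gap shifts of 0.1 to 0.2 between the untreated periods, rejection is about 13% to 45% and 9% to 22% respectively, against a nominal 5%. These figures rest on assumed pre-COVID subgroup rates, 7,800 per period and independent observations. If the odds-ratio gap was constant over the two control periods, all three tests hold 5% and nothing is lost. The figures therefore show what could happen, not what is likely. The stated power above 90% is not in question.

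**What to change.** In section 11.0, Aim 2, replace the general interaction test with one named 1-df contrast from the three-period model: the change in the subgroup gap from the COVID-19 period (15 March to 14 September 2020) to the intervention period (1 November 2020 to 30 April 2021). Apply it to both the White/non-White and the Medicaid comparisons, and state that the Aim 2 test is this contrast. Report the pre-COVID to COVID-19 change in the gap separately, as a description of untreated drift.

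The change costs about a sentence of text and a contrast statement in the same model. It matches the existing power statement (about 97% on the logit scale, about 92% as a risk difference). The price is roughly one point of power against the 2-df test if the control-period gap was constant (97% versus 98%). The text should also acknowledge that the contrast still assumes no untreated drift in the gap after the COVID-19 period.
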